## Abstract

**Background:**

Randomized trials demonstrate that depression care management can improve clinical and work outcomes sufficiently for selected employers to realize a return on investment. Employers can now purchase depression products that provide depression care management, defined as employee screening, education, monitoring, and clinician feedback for all depressed employees. We developed an intervention to encourage employers to purchase a depression product that offers the type, intensity, and duration of care management shown to improve clinical and work outcomes.

**Methods:**

In a randomized controlled trial conducted with 360 employers of 30 regional business coalitions, the research team proposes to compare the impact of a value-based marketing intervention to usual-care marketing on employer purchase of depression products. The study will also identify mediators and organizational-level moderators of intervention impact. Employers randomized to the value-based condition receive a presentation encouraging them to purchase depression products scientifically shown to benefit the employee and the employer. Employers randomized to the usual-care condition receive a presentation encouraging them to monitor and improve quality indicators for outpatient depression treatment. Because previous research demonstrates that the usual-care intervention will have little to no impact on employer purchasing, depression product purchasing rates in the usual-care condition capture vendor efforts to market depression products to employers in both conditions while the value-based intervention is being conducted. Employers in both conditions are also provided free technical assistance to undertake the actions each presentation encourages. The research team will use intent-to-treat models of all available data to evaluate intervention impact on the purchase of depression products using a cumulative incidence analysis of 12- and 24-month data.

**Discussion:**

By addressing the 'value to whom?' question, the study advances knowledge about one of the most pivotal problems in the translation of evidence-based care to 'real world' settings: whether purchasers can be influenced to buy healthcare products on the basis of value and not exclusively on the basis of cost. If value-based marketing increases depression product purchase rates over usual care, this study will provide encouragement to market new healthcare products on the basis of the product's value to the purchaser as well as the recipient of care.

**Trial Registration:**

Clinical Trials Registration Number: NCT01013220

## Background

Recent studies estimate that 7.6% of employees suffer a major depressive episode each year [1]. Depression substantially reduces an employee's ability to work, as evidenced by increased absenteeism [2-5] and reduced productivity at work (hereafter referred to as productivity) [2-7], with annual work costs approaching $24 billion (Y2K$) [1]. As the most prevalent disorder of the five conditions that cause the greatest work loss in the American workforce [8,9], depression will soon become the leading cause of disability in industrialized countries [10].

Employers can reduce their depression-related work losses by ensuring their employees receive the type, intensity and duration of depression care management shown to improve clinical and work outcomes in effectiveness trials [11-14]. Employers, who finance health insurance coverage for an estimated 90% of non-elderly individuals with private health insurance [15], can purchase products that increase the probability that their depressed employees receive this evidence-based care. Interventions to increase product purchase need to increase employer motivation and capacity to purchase.

### Increasing employer motivation to purchase

In the studies to date, employers report substantial information deficits about the costs that organizations absorb when depressed employees fail to receive adequate treatment. Employers who receive this information report interest in reviewing the data that depression products achieve a return on investment. Even more encouragingly, employers note that they are willing to apply program savings from improved absenteeism and productivity against program costs [16-24].

### Increasing employer capacity to purchase

Employers interested in purchasing a depression product that provides value face non-trivial challenges. Employers who contract with multiple health plans have to contract with an additional vendor (*e.g*., a disease management company or managed behavioral health organization) to provide a depression product to their workforce. Because the marketplace does not currently provide a list of vendors who sell depression products, interested employers often know only those products recommended by their colleagues. Not surprisingly, products differ substantially in their cost and capacity to deliver evidence-based services, requiring employers to make informed choices despite imperfect information to realize value for themselves or their employees. To address this need, this study provides technical assistance to employers to identify high-quality depression products, referring to products that provide the type, intensity, and duration of depression care management shown to improve clinical and work outcomes as Depression Management in the Workplace (DMW) products.

### Scope of Study

The specific aims of the study are: to compare the impact of value-based (VB) and usual-care (UC) intervention on employer purchase of depression products; to identify mediators of intervention impact on employer purchase; and to identify organizational-level moderators of employer purchase.

The first specific aim utilizes an experimental design to study intervention effectiveness. Hypothesis one tests whether VB intervention significantly increases purchasing behavior over UC. The second specific aim utilizes a non-experimental design to study intervention mediators. Hypothesis two tests whether intervention impact on purchasing behavior is mediated by the organization's appraisal of product benefit to the employer more than the employee. Hypothesis three tests whether colleagues influence an organization's appraisal of product benefit to employer. The third specific aim utilizes a non-experimental design to study intervention moderators. Hypothesis four tests whether larger and more mature companies with greater financial latitude demonstrate higher levels of purchasing behavior, as well as companies who make greater investments in their employees and have a higher tolerance for benefit risk, independent of intervention. Hypothesis five tests whether companies with de-centralized onsite purchasing groups in which the presentation participant has primary influence will demonstrate higher levels of purchasing behavior, independent of intervention. Hypothesis six tests whether companies with strong vendor relationships demonstrate higher levels of purchasing behavior, independent of intervention.

Before initiating the study, the research team: fully articulated a conceptual framework; pilot tested the VB intervention prototype to demonstrate intervention feasibility, to collect/integrate employer feedback to further strengthen the intervention, and to estimate effect size; created instrumentation to measure intervention mediators, moderators, and outcomes with demonstrated reliability and validity; investigated business coalition interest in participating in the study; and received approval from the Florida State University Institutional Review Board.

## Methods/design

### Participants and setting

#### Regional Coalitions

Employers join coalitions in their geographic area to identify innovative solutions to provide quality healthcare at affordable prices, focusing on benefit products for their non-unionized employees. The 58 coalition members of the National Business Coalition on Health (NBCH) are eligible to participate in the study if: they have 30 or more current employer purchasers as members/affiliates; have hosted presentations in regularly scheduled meetings during the past year (eliminating a limited number of coalitions who served exclusively as purchasing agents); and have not participated in the research team's preliminary studies. The research team, in conjunction with the NBCH Board of Directors, sends eligible coalitions an invitation to participate, followed up by a telephone call, describing the purpose of the study as testing two educational presentations on assuring high quality depression care.

#### Employers

Employers who belong to regional coalitions are eligible to participate if: they represent a public or private company that provides health benefits to 100 or more domestic employees; their company intends to remain in the regional coalition for the next two years; and the coalition's Executive Director does not indicate they have purchased depression products for all their employees in the past two years. Employers who join regional coalitions appoint one employee from their company to represent them. Unpublished studies indicate that more than 60% of these representatives report strong influence in benefit purchasing decisions. The Executive Director of each participating coalition distributes a fact sheet to all eligible representatives inviting them to participate in a study that tests two educational presentations about how companies can improve the depression treatment their employees receive. The Executive Director follows up with each member by telephone to confirm that 6 or more employers agree to participate in the study without knowing which condition they will be assigned to.

#### Randomization

Participating coalitions are randomized to one of six quarters ending March 2011 for presentation to reduce historical threats to validity in non-experimental analyses. As shown in Figure 1, participating employers within a coalition are block randomized by workforce size to the VB or UC condition. After being alphabetized, all participating employers are assigned a unique two-digit number from a random numbers table created by the principal investigator at a centralized location blinded to all company names. Each participating employer is matched to another participating employer in the same coalition by workforce size before the employer with the higher number in each pair is randomized to the VB condition with the other member randomized to the UC condition. When randomization is completed in each coalition, a member of the research team works with the Executive Director to invite participating employers to the presentation to which they had been randomized. Participants remain blind to intervention condition until the presentation begins.

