#### HEDIS presentation

The two-hour HEDIS presentation educates employers about HEDIS indicators for antidepressant medication management and their use in monitoring outpatient depression treatment quality. Employers receive HEDIS indicators for antidepressant medication management for their most subscribed plan if that plan reports its HEDIS scores to the National Committee for Quality Assurance; otherwise, they receive the HEDIS indicators for other plans in the area. During the presentation, employers are asked to encourage their most subscribed health plan to improve its HEDIS indicators for depression (or to calculate its HEDIS indicators if it does not report them). In addition, employers are encouraged to ask their plans to provide individual feedback to clinicians about the quality of their depression care, provide greater formulary access to newer depression drugs, and require lower copayments for outpatient mental healthcare. While causal evidence is lacking, a study reports that these plan characteristics are associated with better HEDIS indicators for antidepressant medication management [26]. Because previous studies indicate that the HEDIS presentation will have little to no impact on employer purchasing [27-31], depression product purchasing rates in the UC condition capture vendor efforts to market depression products to employers in both conditions during follow-up.

The second author [name] provides presentations to both groups. DMW and HEDIS presentation sessions are scheduled for the same day in random order, one in the morning and the other in the afternoon. If after agreeing to be in the study, employer representatives fail to attend the meeting, they are asked to schedule a time in the next four weeks to complete the presentation and data collection individually. If they cannot do so, they are dropped from the study.

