#### Data collection

All employer representatives are asked to complete the pre-presentation survey immediately before the presentation begins, the post-presentation survey immediately after the presentation ends, as well as a 12- and 24-month follow-up survey. Twenty-four-month follow-up surveys are projected to be completed by September 2013. Employers are paid $100 for completing the pre- and post-presentation survey, $100 for completing the 12-month survey, $100 for completing the 24-month survey, and an additional $50 for completing all surveys. Pre- and post-presentation data are collected in the room in which the presentations are delivered using laptop computers. Twelve- and 24-month follow-up data are collected in the subject's office or home using the web. The research team member who actively contacts employers who do not respond to a standardized electronic cue to complete follow-ups is blinded to condition. Pre-presentation data (descriptive characteristics, mediating, moderating, and outcome variables) are collected from employer representatives immediately before the presentation. Post-presentation data (mediating variables and presentation evaluation) are collected from employer representatives immediately after the presentation. Twelve and 24-month data (mediating, selected moderating and outcome variables) are collected in a three month window of the expected timeframe. Employers whose representatives are no longer in the position or with the company are asked to nominate another representative to complete the presentation and remaining follow-up interviews.

The research team also conducts semi-structured interviews with Executive Directors of each participating coalition at baseline (two weeks before the presentation) and at 24-month follow-up. Executive Director baseline interviews provide qualitative data about coalition efforts to encourage VB purchasing. Executive Director follow-up interviews are designed to provide qualitative data on intervention impacts that may not be observable in the structured interviews we conducted with employers, as well as solicit insights from Executive Directors about VB intervention impact and strengthening. Instrumentation is available on the project's website [32].

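### Employers are invited according to their arm by people not said to be blinded, and those who never attend are dropped, so unequal effort could cause selection after randomisation

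*Protocol article*

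**What the plan says.** Entry is concealed. Under Employers, the Executive Director confirms by telephone that at least six employers "agree to participate in the study without knowing which condition they will be assigned to". Under Randomization, the random numbers are produced centrally without sight of company names, and employers are allocated within pairs matched on workforce size.

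Invitation comes next. The same section says that "a member of the research team works with the Executive Director to invite participating employers to the presentation to which they had been randomized", and then: "Participants remain blind to intervention condition until the presentation begins". It says nothing about whether the inviters are blind.

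The section HEDIS presentation covers delivery in both arms. It says that "DMW and HEDIS presentation sessions are scheduled for the same day in random order". Representatives who agreed to take part but miss the meeting are handled as follows: "they are asked to schedule a time in the next four weeks to complete the presentation and data collection individually". The rule then ends: "If they cannot do so, they are dropped from the study". Who asks them is not stated.

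Under Data collection, one staff contact is protected: "The research team member who actively contacts employers who do not respond to a standardized electronic cue to complete follow-ups is blinded to condition". The same section places the first survey immediately before the presentation. Data Analysis specifies intent-to-treat on all available data.

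**The concern.** Four stated facts form a path from arm to analysis set. The invitation is specific to the arm, the inviters are not said to be blind, attendance depends partly on how hard someone pursues it, and non-attendance removes the employer. The Executive Director is also an active party: this person reports prior purchases (which bears on eligibility), distributes the fact sheet and telephones members.

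Consent before allocation and participant blinding stop employers from selecting themselves by arm. They do not stop the inviters from trying harder in one arm. The article guards against a similar risk at follow-up by blinding the person who chases late surveys. The earlier contact, which decides whether an employer stays at all, has no stated guard.

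The damage would be hard to repair later. A dropped employer has neither the pre-presentation survey nor any follow-up. Apart from workforce size, used for matching, the described data collection offers little with which to test or adjust for selective loss.

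**Working it through.** **The plan's own figure.** 360 × (1 − 0.20) / 2 = 144 per group, as stated. For a 0.35 SD difference, the noncentrality is 0.35 × √(144/2) = 2.97, and power is Φ(2.97 − 1.96) = 84.4% (84.1% by noncentral t). This is within two points of the stated 86%, and the present point does not depend on it.

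**Inputs from the documents.** Target effect 0.35 (Data Analysis); 360 employers in 30 coalitions (Abstract); allocation within pairs. This averages 360/30 = 12 employers per coalition, or about 6 per arm, so one lost employer is about 1/6 = 17% of a coalition's arm.

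**Assumed inputs, with no source in the documents.** A share q = 0.30 of employers is reluctant to attend. Their mean on the purchasing-behaviour scale (EBPB) is δ = 0.5 to 0.8 SD below the rest. A share r of the reluctant is secured, and all others attend. The true effect is zero.

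**Formula.** Relative to non-reluctant employers, the mean among attenders is −δ × q·r / (q·r + 1 − q). The bias in VB minus usual care (UC) is therefore δ × (f_UC − f_VB), where f = q·r / (q·r + 1 − q).

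| r in UC | r in VB | f_UC | f_VB | bias, δ = 0.5 | bias, δ = 0.8 |
|---|---|---|---|---|---|
| 0.85 | 0.80 | 0.255/0.955 = 0.267 | 0.240/0.940 = 0.255 | +0.006 | +0.009 |
| 0.85 | 0.70 | 0.267 | 0.210/0.910 = 0.231 | +0.018 | +0.029 |
| 0.90 | 0.50 | 0.270/0.970 = 0.278 | 0.150/0.850 = 0.176 | +0.051 | +0.082 |

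As shares of the 0.35 target: 0.006/0.35 = 2%, 0.029/0.35 = 8%, and 0.082/0.35 = 23%.

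**Direction.** In every row, reluctant employers are secured more often in UC, which lowers the UC mean and favours VB. Exchanging the two values of r changes the sign: more effort on reluctant VB employers biases against VB.

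**Effect on type I error.** Suppose a fraction d is lost from VB only, scoring g SD below those kept. The bias is d × g, with standard error √(1/[144(1 − d)] + 1/144).
- d = 5%, g = 0.5: bias 0.025 SD, two-sided type I error 5.5%.
- d = 15%, g = 0.5: bias 0.075 SD, type I error 9.4%.
- d = 20%, g = 1.0, a stress case: bias 0.20 SD, type I error 36%. It requires a fifth of VB to be lost with no loss in UC, which attendance counts would expose.

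**The case against.** The strongest reply is that the article never says outright that the inviters know the arm. Employers stay blind until the talk begins, so invitations cannot name the talk. With both sessions on one day in random order, this suggests that invitations already refer to a morning or afternoon slot. Whether the inviters hold the key to those slots is an operational detail that a condensed article might leave out. This stands in part: knowledge of the arm is the plain reading, not a stated fact, and one sentence could settle it. But the article does describe invitation by randomised presentation and states blinding at that step for participants only, so this is more than silence.

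Second, the scope for steering is limited. Employers agreed before allocation, are offered a make-up session and are paid for completing surveys. The 0.08 SD case needs overall attendance of 0.70 + 0.27 = 97% in UC against 0.70 + 0.15 = 85% in VB, a visible gap. This stands, and is why the likely size is small.

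Third, the bias works only through the drop rule. If non-attenders were followed and analysed, the selection would vanish whoever did the inviting. This also stands. Blinding the inviters keeps arm-dependent effort from shaping attendance; it does not cure the dropping of randomised employers.

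A reader might infer more: that attendance was in fact steered, that the bias must favour VB, that the Executive Director knows employers personally, or that the Executive Director arranges the make-ups. The documents support none of these. They give no attendance by arm and no reason to expect less effort in VB. They show only telephone contact and knowledge of purchases, and do not say who arranges make-ups.

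**Conclusion.** The point holds as a risk of bias. As described, invitation follows the arm assignment, the inviters are not said to be blinded, and employers who never attend are removed, so arm-dependent effort could alter who is compared. The size cannot be determined from the documents. With 30% reluctant employers and a 0.5 to 0.8 SD gap, it is about 0.01 to 0.03 SD for modest differences in effort and about 0.08 SD (23% of the target) in the extreme case of that model. All these figures rest on assumed inputs, and the sign depends on which arm secures more of its reluctant employers. The change is worth making because it costs little and the lost information cannot be recovered afterwards.

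**What to change.** - **Randomization section.** State that invitations and reminders carry only a group code and a time slot, and that the random draw of which talk fills which slot is sealed from the Executive Director and the inviting staff until the sessions start. If this is already the practice, one sentence saying so is enough.
- **Missed-meeting rule (HEDIS presentation section).** Arrange make-up sessions by a fixed script, with the same number and timing of contact attempts in both arms. Sealing no longer helps here, because the slot order is known after session day. For the same reason, do not use the blinded follow-up contact, who could be unblinded before the outcome surveys.
- **Reporting.** Report attendance and make-up completion by arm, including for sessions already held.
- **Analysis set.** Separately, keep every randomised employer in follow-up and in the intent-to-treat analysis. The steps above complement this and do not replace it.

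The cost is small. Both talks already run on one day in random order. The presenter must have both ready for either slot, and contact attempts must be logged. The company-specific return estimates and plan-specific HEDIS scores would have to be prepared by someone outside the inviting staff.

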**Figure 1 F1:**
[figure not shown]
**Research Design**.

#### Intervention

The intervention consists of a presentation and technical assistance delivered to employer representatives at local meetings sponsored by regional coalitions. Employers randomized to the VB condition receive the Depression Management in the Workplace (DMW) presentation. Employers randomized to the UC condition receive the Healthcare Effectiveness Data and Information Set (HEDIS) presentation. All interested employer representatives are offered condition-specific technical assistance free of charge during the 24 months after the presentation.

